## Abstract

**Methods and analysis::**

This study was conducted as a multicenter randomized control trial (RCT) in 8 high-volume medical centers in Japan, and will prove the non-inferiority of bilateral drainage to trisegmental drainage. Patients with unresectable HMBO with Bismuth type IIIa or IV who pass the inclusion and exclusion criteria will be randomized to receive bilateral or trisegmental drainage at a 1:1 ratio. At each center, the on-site study investigators will obtain informed consent from the candidates, and will use an electronic data capture system (REDCap) to input necessary information, and register candidates with the registration secretariat. The primary endpoint is the rate of non-recurrent biliary obstruction (RBO) at 180 days after SEMSs placement. A −10% non-inferiority margin is assumed in the statistical analysis of the primary endpoint. Secondary endpoints include the rate of technical and clinical success, time to recurrent biliary obstruction (TRBO), causes of RBO, procedure-related adverse events (AEs), procedure time, TRBO with or without endoscopic sphincterotomy, overall survival, and the technical and clinical success rates at reintervention.

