### 2.9. Sample size calculation

The primary endpoint of this study is the stent non-RBO rate. According to the results of our past study,^[9]^ the non-RBO rate of the bilateral drainage group was 72.3% with a 95% confidence interval: CI 55.8% to 84.9%. The non-RBO rate of the trisegmental drainage group was 52.9% with a 95% CI 42.4% to 63.2%. Based on this, the expected value of the non-RBO rate of bilateral drainage group is set at 72.3%, and that of trisegmental drainage group is set at 52.9%. We set the non-inferiority margin as 10%. Assuming testing with a one-sided α value of 0.05 using the exact method assuming a binomial distribution under the above set values, 33 cases are required for detection with a statistical power of 80%. Considering the exclusion/dropout rate of about 15%, the target number of cases is set at 76 cases.

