### 2.10. Statistical analysis

The full analysis set (FAS) was defined as all randomized cases excluding minimally excludable cases. Minimally excludable cases were defined as follows: Ineligible subjects who were incorrectly enrolled, cases in which the drainage treatment itself was not performed after allocation, cases in which all post-assignment outcome data are missing, and cases in which consent is withdrawn. The population of the FAS who complete treatment is defined as the per protocol set (PPS). This includes cases in which the treatment complies with the allocation, without missing data, and without serious protocol violations.

Intention-to-treat (ITT) and per-protocol (PP) methods are used for the analysis. The ITT analysis is the main analysis based on the FAS, whereas the PP analysis is a sub-analysis based on the PPS. Demographic and clinical characteristics will be presented as the median (interquartile range) for continuous variables and frequency (percentage) for categorical variables. Welch’s *t* test and a χ^2^ test will be used to compare continuous and categorical variables, respectively.

The primary endpoint analysis will be performed according to the ITT principle. A point estimate of the difference between the non-RBO proportion in the bilateral drainage group and the trisegmental drainage group and its 95% Wald confidence interval will be calculated. Non-inferiority is considered statistically significant when the lower limit of 95% CI exceeds the non-inferiority margin of 10%, or when the *P* value is less than 5%.

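### The success rule in section 2.10 carries a sign slip in the margin and joins by 'or' two criteria that can disagree; one criterion should stand

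*Protocol article*

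**What the plan says.** Section 2.10 defines the primary contrast as "A point estimate of the difference between the non-RBO proportion in the bilateral drainage group and the trisegmental drainage group", with a 95% Wald interval. Non-RBO is the favourable outcome, so positive values favour bilateral drainage. The success rule follows: "Non-inferiority is considered statistically significant when the lower limit of 95% CI exceeds the non-inferiority margin of 10%, or when the". The second route, which the sentence goes on to name, is a P value under 5%. Section 2.10 does not say which null hypothesis this P value tests, or whether it is one- or two-sided.

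Two other places bear on the rule. The abstract gives the margin a sign: "A −10% non-inferiority margin is assumed in the statistical analysis of the primary endpoint". Section 2.9 gives it without one ("We set the non-inferiority margin as 10"%) and fixes the test level: "Assuming testing with a one-sided α value of 0.05 using the exact method assuming a binomial distribution". The closing lines on statistical analysis give a significance level of 5% without sidedness.

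**The concern.** This sentence alone decides whether the trial is positive, and it is faulty in two respects.

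- **Sign.** For a difference where higher favours bilateral drainage, non-inferiority means a lower limit above −10 points. A lower limit above +10 points would be a claim of superiority by more than 10 points.
- **Two routes.** The interval half works at one-sided 2.5% and the P half at 5%. If they disagree, 'or' lets either one carry the claim. A result between the two thresholds would be open to dispute in an open-label trial whose planners expect bilateral drainage to do better.

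In addition, the P value is not tied in that sentence to the −10 point null.

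**Working it through.** **Inputs.** From section 2.9: expected non-RBO 72.3% (bilateral, p_B) and 52.9% (trisegmental, p_T), margin 10 points, one-sided alpha 0.05, power 80%, 33 cases, dropout about 15%, total 76. From section 2.6.3: 1:1 allocation. From section 2.10: 95% Wald interval. That 33 is per arm is inferred from the total of 76.

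**1. Reproducing the sample size.** Let L be the value that the lower limit must exceed.

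n per arm = (z_{1−α} + z_{0.80})² × [p_B(1−p_B) + p_T(1−p_T)] / (p_B − p_T − L)²

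Variance sum: 0.723×0.277 + 0.529×0.471 = 0.2003 + 0.2492 = 0.4494.

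- L = −0.10, one-sided 0.05: (1.645+0.842)² × 0.4494 / 0.294² = 32.1, so **33**. This is the plan's figure.
- L = −0.10, one-sided 0.025: (1.960+0.842)² × 0.4494 / 0.294² = 40.8, so 41.
- L = +0.10 (denominator 0.094²): 315 at one-sided 0.05 and 400 at one-sided 0.025.

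Dropout: 33 × 1.15 = 37.95, so 38 per arm and 76 in total. Of these four settings, only a limit of −10 points with one-sided 0.05 gives 33.

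**2. The two halves on one scale.** Take the limit at −10 points and the P value as the one-sided non-inferiority test of section 2.9. With z = (d + 0.10)/SE, the interval half requires z > 1.960. The P half requires z > 1.645, which is the same as a lower 90% limit above −10 points. Every result that passes the first also passes the second, so the 'or' rule is the 90% rule.

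**3. A result in the gap.** Take 22/33 (66.7%) against 18/33 (54.5%).

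- d = 0.121; SE = √[(0.667×0.333 + 0.545×0.455)/33] = 0.119.
- Lower 95% limit: 0.121 − 1.960×0.119 = −11.3 points. Fails.
- One-sided P against −10 points: z = 0.221/0.119 = 1.85, P = 0.032. Passes (lower 90% limit −7.5 points).

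**4. Size of the gap.** Success at a true −10 points (42.9% against 52.9%) is by full binomial enumeration. Power at the planning rates is by enumeration and by the normal formula Φ(0.294/SE − z), with SE = √(0.4494/n) = 0.117 at 33 and 0.109 at 38 per arm.

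| Rule, limit at −10 points | Success at true −10, 33 / 38 per arm | Power, 33 per arm | Power, 38 per arm |
|---|---|---|---|
| 95% interval | 2.7% / 2.8% | 71% | 77% |
| One-sided P < 0.05 (90% interval) | 4.7% / 4.7% | 80–81% | 84–86% |

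At another location of the null (62.3% against 72.3%, 33 per arm) the two success figures are 2.8% and 5.2%.

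**5. Other readings of the P value, 33 per arm.**

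- Two-sided test against −10 points: in the favourable direction it equals the 95% interval. It would also admit results significantly below −10 points (3.6% at a true −10).
- Two-sided test of no difference: 9/33 against 18/33 gives d = −27 points, 95% interval −50 to −4.5, P = 0.024. It would meet the P half although bilateral drainage is significantly worse.

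**The case against.** The best defence is that the rest of the article settles most of this. The abstract writes −10%, quoting a margin without its sign is common, the stated aim is non-inferiority, and the sample size follows only from −10 points. The P value in a sentence about non-inferiority is naturally that of the non-inferiority test, whose margin, level and sidedness are in section 2.9. On that reading the P half runs at the planned alpha, and it is the 95% interval that departs from the plan.

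Most of this stands, and it rules out three stronger inferences that a reader might draw.

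- *The trial has only 12–15% power at 33 per arm because the limit is +10 points.* That is the power of the literal interval half alone. Under the whole literal rule, with section 2.9's one-sided P, the P half governs and power is 79.5% at 33 and 84% at 38 per arm.
- *The rule would often declare a worse treatment non-inferior.* If the P value came from the chi-squared test of no difference, significance against bilateral drainage would occur at 38 per arm in 42% of trials at a true −20 points and 14% at a true −10. The arithmetic is right, but the reading is unlikely. The chi-squared test is named next to the description of patient characteristics, before the primary-endpoint paragraph.
- *The type I error is double what was planned.* One-sided 5% is the planned level. The P half is looser than the 95% interval, not looser than the design.

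The defence does not remove the conflict between the two halves. A 95% interval and a one-sided 5% test are different criteria, and the sentence accepts either.

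**Conclusion.** The rule is wrong as written and has to be corrected before analysis. The sign is a drafting slip that the abstract and the sample size already resolve. The substantive fault is the pairing of a one-sided 2.5% criterion with a 5% one. Its size is the band between the 95% and 90% lower limits: 2.7% against 4.7% success at a true −10 points, and about 71% against 80% power, at 33 per arm. The missing link between the P value and the −10 point null is a lesser gap, which the same correction closes.

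This rests on 33 being per arm, on the difference being bilateral minus trisegmental (the order of the wording), and on P values computed with the same Wald standard error as the interval. Section 2.9 names an exact method, whose P values would differ somewhat. That would move the edge of the band but would not make the two halves agree.

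**What to change.** State one criterion, delete the P-value alternative, and write the limit as −10 percentage points for bilateral minus trisegmental. Two versions are workable.

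- **(a) Keep the planned one-sided alpha of 0.05.** Suggested text: Non-inferiority is concluded if and only if the lower limit of the two-sided 90% confidence interval for the difference in non-RBO proportion (bilateral minus trisegmental) is above −10 percentage points. This matches 33 per arm and about 80% power, and costs one sentence.
- **(b) Keep the 95% interval (one-sided 0.025), limit at −10 points.** Section 2.9 must then be restated: one-sided 0.025, with power about 71% at 33 and 77% at 38 per arm. Restoring 80% needs about 41 evaluable per arm. With dropout that is 41 × 1.15 = 47.15, so 48 per arm and 96 in total (or 41/0.85 = 48.2, so 49 per arm and 98), against 76 planned.

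Under either version, any reported P value should be the one-sided test against −10 points at the same alpha. The choice should be fixed and dated before outcome data are compared by arm.

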### 2.11. Adverse event reporting

The principal investigator of the institution where the serious AE occurs should take appropriate measures, regardless of whether or not there is a causal relationship with the research, and should immediately report the details of the event to the head of the research institution and the principal investigator, in accordance with the regulations of the respective medical institution. A serious adverse event is an AE occurring during the procedure or any time after the procedure that fulfills ≥ of the following criteria:

Results in death or is immediately life-threatening.Requires in-patient hospitalization or prolongation of existing hospitalization (≥10 days).Results in persistent or significant disability or incapacity.A congenital abnormality or birth defect.

### 2.12. Monitoring

Off-site monitoring (using e-mail, web meeting tool, electronic data capture system) will be carried out 30% of enrolled patients throughout the trial by an independent data monitoring unit. The monitoring unit will collect information on the status of accumulation, inclusion/ exclusion criteria, serious AEs, and any other relevant information, and strive to provide feedback to participating institutions for early resolution if there are any problems. The monitoring committee will also report any serious AEs to the committee for efficacy and safety assessment. Data quality check will be performed using an electronic data capture system every 6 months by an independent unit. Auditing will not be performed in this study.

## 3. Discussion

Bilateral endoscopic drainage with SEMS can be used to effectively manage patients with HMBO.^[1–5]^ However, few reports have described the utility of trisegmental drainage and the benefits of using trisegmental drainage remain unknown.^[6–9]^ There have been no RCTs to compare bilateral and trisegmental drainage in patients with high-grade HMBO. The primary endpoint of this multicenter RCT is the comparison of the non-RBO rate at 6 months between bilateral and trisegmental drainage in patient with high-grade HMBO. The secondary endpoints are the rates of technical and clinical success, procedure time, procedure related AEs, TRBO, technical and the clinically successful reintervention, and overall survival in the two groups. If the non-inferiority of bilateral drainage is demonstrated, it is predicted that the procedure time will be shortened, and medical costs will be reduced.

Recent studies have reported that the technical success rate and stent patency in patients with HMBO treated with bilateral drainage using SEMS were 90% to 100% and 4.2 to 16.3 months, respectively.^[2–5]^ Only three previous studies have been published on trisegmental drainage using three SEMSs; these reported technical success rates and stent patency of 82% to 100% and 5.7 to 7.1 months, respectively.^[6–9]^ Each study was associated with some limitations, the benefit of trisegmental drainage is not clear. In our previous study, we compared stent patency between bilateral and trisegmental drainage in patients with HMBO limited to Bismuth IIIa or IV; however, the study was associated with some limitations.^[9]^ First, this was a retrospective study that included a small number of patients in the bilateral drainage group. Second, the decision to perform bilateral or trisegmental drainage was left to the discretion of each physician. Third, although most cases underwent drainage using the PSIS method, three drainage methods were utilized. Finally, various devices, SEMSs, and PSs were used.

This study will resolve the limitations of previous studies. We believe that this RCT will be able to correctly assess the study endpoints.
